## Abstract

**Background:**

Two strategies of the US Ending the HIV Epidemic initiative are early diagnosis of infections via widespread testing and prevention of new infections using pre-exposure prophylaxis (PrEP). These strategies are particularly important for adolescents and young adults (AYAs) who are disproportionately affected by HIV, particularly if they identify as Black and/or lesbian, gay, bisexual, transgender, queer or questioning, and others (LGBTQ+). This study will develop and test an interactive life-simulation game in which players can enact real-life behaviors and receive their HIV risk profile to improve HIV testing and PrEP access among AYAs aged 13-24 years in Washington, DC.

**Objective:**

This mixed methods study aims to determine the acceptability of an interactive, enhanced life-simulation game prototype among AYAs, conduct a pilot test of the gaming intervention among a small cohort of AYAs to ensure game usability and acceptability, and evaluate the efficacy of the game in a randomized controlled study with AYAs at risk for HIV in Washington, DC.

**Methods:**

This research protocol will be conducted in 3 phases. A formative phase will involve surveys and focus groups (n=64) with AYAs living in the DC area. These focus groups will allow researchers to understand youth preferences for game enhancement. The second phase will consist of a pilot test (n=10) of the gaming intervention. This pilot test will allow researchers to modify the game based on formative results and test the planned recruitment and data collection strategy with intended end users. The third phase will consist of a randomized controlled study among 300 AYAs to examine the efficacy of the life-simulation game compared with app-based HIV educational materials on HIV and PrEP in changing HIV testing, knowledge, risk behaviors, and PrEP access. Participants will have unlimited access to either the life-simulation game or the educational app for 3 months from the time of enrollment. Study assessments will occur at enrollment and at 1, 3, and 6 months post enrollment via e-surveys. At 6 months, a subset of intervention participants (n=25) will participate in in-depth *exit* interviews regarding their experience being in the study.

**Results:**

Institutional review board approval was received on February 5, 2020. This project is currently recruiting participants for the formative phase.

**Conclusions:**

This interactive life-simulation intervention aims to increase HIV testing and PrEP access among AYAs in the DC area. In this intervention, players can enact real-life behaviors and receive their HIV risk profile to promote HIV testing and PrEP seeking. Such an intervention has great potential to improve knowledge of HIV and PrEP among AYAs, increase motivation and self-efficacy related to HIV testing and PrEP use, and decrease individual and structural barriers that often preclude engagement in HIV prevention services.

**Trial Registration:**

ClinicalTrials.gov NCT04917575; https://clinicaltrials.gov/ct2/show/NCT04917575

**International Registered Report Identifier (IRRID):**

PRR1-10.2196/29792

## Introduction

### Background

The goals of the US National HIV AIDS Strategy, Ending the HIV Epidemic initiative, and the HIV care continuum to reduce new HIV infections by intensifying prevention efforts where HIV is most heavily concentrated [1-3] are particularly important for adolescents and young adults (AYAs) aged 13-24 years who are disproportionately impacted by HIV. In 2018, AYAs accounted for 21% of new HIV infections, and young men who have sex with men (YMSM) and transgender women who identified as Black or Latinx were most severely affected [4]. In Washington, DC, a geographic hotspot for HIV [3], AYAs accounted for 21% of new diagnoses in 2019 [5]. Furthermore, Black youth and YMSM in DC accounted for 75% and 60% of new HIV diagnoses among youth in 2019, respectively [6]. Thus, creative strategies to support risk assessment, prevent HIV infection, encourage routine HIV testing, and link AYAs to care are increasingly paramount.

Barriers to HIV testing among youth include difficulty identifying and accessing HIV testing sites, low health literacy and beliefs that HIV remains a severe and fatal disease, and lack of self-perceived risk for HIV [7-12]. Aside from HIV testing, the use of other HIV prevention interventions, such as pre-exposure prophylaxis (PrEP), has been limited among AYAs. Hence, there is a need to improve youth understanding of HIV, how to prevent it, and behaviors that put one at risk for infection and to provide them with resources to access HIV testing and PrEP, in a youth-friendly and nonjudgmental manner [8,13,14]. A review of HIV testing interventions focused on increasing adolescents’ intentions to obtain HIV testing found that facilitators of testing include understanding testing as an essential part of accessing early treatment, helping youth think about future health, and learning how to effectively communicate with their sexual partners [12]. Furthermore, with the US Food and Drug Administration expansion of PrEP to adolescents and the US Preventive Services Task Force Grade A recommendation for PrEP, options for HIV prevention interventions for AYAs have expanded [15-17].

Despite the fact that AYAs are more receptive to HIV information when it is provided in an entertaining format [12,18] and when the material comes from a peer [19-21] or is shared over social media, interventions to promote HIV testing among AYAs have been limited. Digital game–based interventions are a potential strategy to increase HIV testing among AYAs as they overcome traditional barriers faced by this group [22] and can educate while simultaneously motivating AYAs [23]. In addition, paradata, or information related to the process of data collection, can be used to assess the levels of intervention exposure and can assist in further tailoring interventions to individual AYAs. Paradata can potentially inform which elements of HIV interventions are most useful, should be modified, or removed to increase an intervention’s efficacy and can assist in tailoring game-based interventions in a timely and cost-effective manner [24].

### Theoretical Framework for Intervention

We will use social cognitive theory (SCT) and the health belief model (HBM) to ground our intervention development. SCT provides a framework relevant to both health behaviors and interventions and has been widely used in HIV interventional studies [24-27]. We hypothesize that the game intervention will positively influence youth self-efficacy, risk perceptions, and knowledge of HIV prevention as well as influence AYAs’ social support. The HBM proposes that health behaviors are influenced by a person’s perceived susceptibility and seriousness of a disease and the benefits of acting to reduce that risk [28]. HBM has been used to assess HIV testing uptake among various populations, including AYAs [29-32]. We expect that as AYAs navigate and experience the various game scenarios, encounter persons of different HIV risk, and learn about HIV and associated risks, the game will increase HIV risk perception, increase HIV and PrEP knowledge, and improve self-efficacy with respect to sexual relationships and HIV prevention, that is, seeking HIV testing, PrEP, or reducing risky sexual behaviors.

### Aims and Objectives

This mixed methods study will enhance a life-simulation game intervention for AYAs at risk for HIV in the Washington, DC, metropolitan area. The game will be informed by findings from the focus groups with 64 AYAs. We will then conduct a pilot test with 10 AYAs and a randomized controlled trial (RCT) with 300 AYAs. To evaluate the efficacy of the life-simulation game compared with app-based HIV educational materials on HIV and PrEP in changing HIV testing, knowledge, risk behaviors, and PrEP access, RCT participants will have unlimited access to either the game or the educational app for 3 months from the time of enrollment. Electronic study assessments will occur at enrollment and at 1, 3, and 6 months post enrollment. At 6 months, a subset of intervention participants (n=25) will participate in in-depth *exit* interviews regarding their experience being in the study.

## Methods

### Participants

AYAs will be eligible for enrollment in each phase of the study based on the following criteria: (1) ages 13-24 years; (2) English speaking; (3) sexually active; (4) HIV-negative status; (5) residing in DC, Maryland, or Virginia; and (6) able to provide informed consent or assent. AYAs participating in the second and third phases will also need to have a mobile phone that they are willing to use for the study. We are limiting the study to AYAs aged 13-24 years because they account for a significant proportion of new HIV cases in Washington, DC, and doing so will allow for the development of a life-simulation gaming intervention that is targeted, acceptable, and engaging for this specific population. We plan to enroll a sample representative of diverse racial and ethnic and sexual behaviors.

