Focus group questions cover the following topics: HIV and PrEP knowledge, perceptions and experiences regarding HIV testing, current use of and access to gaming technology (eg, use of smartphones, game consoles), perceptions regarding game enhancements and their potential role in increasing HIV testing and access to PrEP, perceptions about the role of social media and its influence on HIV testing behaviors, and opinions regarding effective recruitment approaches through social media. The enhanced life-simulation game will be demonstrated to participants, and feedback will be elicited regarding the acceptability and relevance of characters, texts, actions, and graphics, as they relate to race, culture, and structural factors. Following the focus group, participants will be sent the link to a survey in REDCap to assess their change in knowledge of HIV and PrEP as well as their satisfaction with the game prototype.

All focus groups will be audio recorded, and a verbatim transcription is professionally produced. The resulting text file will be entered into the qualitative data analysis software Atlas.ti 7.0 (ATLAS.ti Scientific Software Development GmbH) and analyzed using an a priori and open coding process aimed at identifying relevant themes and categories to inform the development of the game modifications for round 2 focus group testing as well as the final game prototype in the pilot test. Key decisions will include potential differences by age and sexual orientation, the types of games, art styles, social features, type or frequency of in-game bonuses, and responses of different kinds of in-game virtual rewards for actions such as demonstrating knowledge of HIV risks and virally spreading the game to peers. Game modifications will be made based on the initial focus group feedback (n=32), after which the second group of participants (n=32) will be recruited and shown the revised game. Survey data will be cleaned, downloaded, and exported into Excel or SAS files, and descriptive statistics will be analyzed. Pre- and postgame knowledge levels will be calculated; however, because of the small sample size, no statistical testing will be performed.

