#### User Field Testing

Pilot test participants will be recruited via advertisements placed on various social media sites. Interested participants will be directed to a web-based eligibility screener in REDCap. Participant eligibility will be confirmed by the project staff via phone. Eligible participants will provide electronic consent and assent and complete the baseline survey electronically via a HIPAA-compliant participant management database. Participants will then be sent the gaming app electronically to download on their phone and will have unlimited access for 1 month. User pilot testing will allow project staff to identify any unanticipated issues with game log-ins, navigation, functionality, paradata collection, or other unforeseen technical issues. During user testing, game use as well as HIV testing and PrEP locator use will be monitored and paradata will be accessed for a 1-month period.

We will also pilot the use of the HIPAA-compliant participant management database for participant screening, survey collection, and data management and troubleshoot for any issues with phone connectivity, data caching, paradata collection, or other potential issues. Baseline data on HIV testing and knowledge will be collected to preliminarily describe the anticipated characteristics of our web-based sample. Measures of game satisfaction [35], usability [36], and a modified version of the motivation, attitude, knowledge, and engagement instrument [37] will also be piloted to determine how well the game addresses HIV knowledge and testing. At the end of the 1-month period, brief surveys and in-depth interviews (IDIs) will be conducted with the 10 pilot participants to elicit features of the games that worked well and identify those that might prohibit full use of the intervention.

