### Randomized Controlled Trial

#### Overview

We will evaluate the impact of the life-simulation game compared with app-based HIV educational materials in an RCT with 300 AYAs. To enroll a sample representative of diverse racial or ethnic and sexual behaviors as well as a sample of non–clinic-attending AYAs, recruitment will occur primarily through social media. We will place targeted advertisements toward YMSM and Black and Hispanic AYAs on social media sites, such as Facebook, Instagram, and Snapchat. In addition, we will provide recruitment materials with quick response codes to the DC Health and Montgomery county school-based health programs. Interested AYAs will click on an advertisement and be directed to a web-based eligibility screener to determine their age, gender, sexual behaviors and orientation, state of residence, and availability of a reliable cell phone. The eligibility of the participants will be confirmed by the project staff via phone. Eligible participants will then provide electronic consent and complete the baseline survey electronically. Participants will be randomized using the block randomization method designed to ensure groups of equal sample sizes (1:1). Participants will be randomized in blocks of 6, stratified by age (13-17 years and 18-24 years) and sexual behavior (LGBTQ+ vs heterosexual), using a random number generator for assignment. Randomization will occur through the HIPAA-compliant participant management database platform. We will compare conditions on HIV testing, knowledge, risk behaviors, and PrEP access at enrollment and at 1, 3, and 6 months post enrollment via electronic survey assessments. At 6 months, a subset of intervention participants (n=25) will participate in in-depth *exit* interviews regarding their experience being in the study. A schematic of the study design is shown in Figure 5.

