	**Game and paradata**				
		Game downloads		✓	✓
		Frequency and duration of game play		✓	✓
		Game satisfaction [35]		✓	✓
		Usability [36]		✓	✓
		Teaching approach [37]		✓	✓
		CDC^f^ Risk Estimator scores		✓	✓
		Number of linkages to HIV testing locator		✓	✓
		Number of linkages to PrEP locator		✓	✓
		Recommend app to friend or share on social media		✓	✓

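### The RCT eligibility rule admits focus-group and pilot participants who have already seen or played the game, and rewarded peer sharing is contemplated although individuals are randomised; the dilution is probably small and cheap to prevent

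*Protocol article*

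**What the plan says.** **Eligibility.** Under Participants, the article states: "AYAs will be eligible for enrollment in each phase of the study based on the following criteria". Six criteria follow. The only addition for the later phases is: "AYAs participating in the second and third phases will also need to have a mobile phone that they are willing to use for the study". In the RCT Overview, interested youths are "directed to a web-based eligibility screener to determine their age, gender, sexual behaviors and orientation, state of residence, and availability of a reliable cell phone", and staff then confirm eligibility by phone. Neither the list nor the screener items mention earlier participation or earlier contact with the game.

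**Earlier exposure.** In the Formative Focus Groups (two rounds of 32): "The enhanced life-simulation game will be demonstrated to participants". In User Field Testing (10 youths): "Participants will then be sent the gaming app electronically to download on their phone and will have unlimited access for 1 month". All three phases cover the same area and rely mainly on social media to recruit.

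**Sharing.** Among the design decisions that the focus groups will inform are responses to "in-game virtual rewards for actions such as demonstrating knowledge of HIV risks and virally spreading the game to peers". Table 1 ticks "Recommend app to friend or share on social media" as a measure for the pilot and the RCT.

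**Trial design.** Participants are individually randomised 1:1 in blocks of 6. For the RCT, social media advertising is supplemented as follows: "we will provide recruitment materials with quick response codes to the DC Health and Montgomery county school-based health programs". The Statistical Analysis section allows for 16% attrition and makes no allowance for controls being exposed to the game.

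**The concern.** A control participant who has already seen or played the game has received part of the intervention. There are two routes.

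- **Re-entry from an earlier phase.** This exposure comes before randomisation. It falls on both arms alike in expectation, so it creates no imbalance, but exposed controls are no longer a game-free comparator.
- **Peer sharing during the RCT.** This comes after randomisation and could carry the game from intervention participants to controls they know.

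Both push the 6-month difference in HIV testing towards zero, and an intention-to-treat analysis keeps that dilution. The article itself treats brief contact as potentially active: focus-group members are surveyed afterwards for change in HIV and PrEP knowledge, which are secondary outcome domains in the RCT. Its Introduction also says that youths are more receptive to material from peers or social media.

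**Working it through.** **Inputs from the Statistical Analysis section.** Control rate 10%; difference 13 points, so 23% in the intervention arm; 150 per arm; 16% attrition; two-sided 5% test. Analysed per arm: 150 × 0.84 = 126.

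**Step 1: reproduce the stated power (above 80%).** Normal approximation for two proportions:

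power = Φ[(d − 1.96 × SE0) / SE1], where SE0 = √(2 × p̄(1 − p̄)/n) and SE1 = √((p1(1 − p1) + p2(1 − p2))/n).

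With p1 = 0.10, p2 = 0.23, p̄ = 0.165 and n = 126: SE0 = 0.04676, SE1 = 0.04604, and (0.13 − 1.96 × 0.04676)/0.04604 = 0.833, so power = 79.8%. Exact enumeration of the uncorrected chi-square test gives 80.3%. The stated figure is reproduced at its boundary, with practically no reserve.

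**Step 2: limits on re-entry.**

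- All earlier participants: 64 + 10 = 74, and 74/300 = 24.7%. This needs every one of them to re-enrol.
- Pilot players only: 10/300 = 3.3%, or about 5 of the 150 controls.
- Through re-entry alone with even allocation, 5% of controls (7.5 of 150) needs 15 of the 74 to return (20%); 10% (15 of 150) needs 30 of the 74 (41%).

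**Step 3: dilution.** The article gives no contamination rate, so the share c of exposed controls is an assumption, as is the premise that each takes on the full game effect. Then control rate = 0.10 + 0.13c, with the intervention rate held at 23% and 126 analysed per arm.

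| c | Control rate | Difference (points) | Power |
|---|---|---|---|
| 0 | 10.0% | 13.0 | 79.8% |
| 3.3% (all 10 pilot players) | 10.4% | 12.6 | 76.5% (77.0% exact) |
| 5% | 10.65% | 12.35 | 74.8% |
| 10% | 11.3% | 11.7 | 69.5% |
| 24.7% (all 74) | 13.2% | 9.8 | 52.4% |

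The last row is a ceiling for re-entry, not a forecast: 64 of the 74 saw only a demonstration, so giving them the full effect overstates the dilution.

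**The case against.** The strongest reply is that this is an argument from silence in a condensed article: re-enrolment rules and app access controls may be in the full protocol, and nothing in the article invites re-enrolment. That stands for access controls. It carries less weight for eligibility, which the article sets out as an explicit numbered list with one named addition for the later phases. If the full protocol has an exclusion, confirming it settles that part.

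The article also points towards controlled access. User Field Testing mentions game log-ins; Intervention Delivery gives the game to intervention participants; Control Condition sends controls a link to a different app; and the Conclusions make wider release conditional on effectiveness. None of this establishes closed access, but it lowers the likely size. Controls also receive the risk estimator and the locators by design, so part of the game's content is in the comparator already.

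A reader might infer three stronger things, none of which the article supports:

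- **That earlier exposure unbalances the arms.** It precedes randomisation and balances in expectation.
- **That rewarded sharing will operate in the RCT.** It is a design topic for the focus groups. The Table 1 item measures recommending or sharing and does not show that a share gives anyone access.
- **That friends recruited through schools will be split between arms.** This is possible, but recruitment is mainly through social media and nothing shows such clustering.

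Individual randomisation remains a legitimate choice.

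**Conclusion.** The point holds as a cheap improvement to the design. On the stated criteria, focus-group and pilot participants are eligible for the RCT and can be allocated to control, and the article contemplates rewarded peer sharing in an individually randomised trial.

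The size is unknown and probably small. The firmest bound is for the pilot players: at most 3.3% of the sample, taking power from about 80% to about 77% if all 10 re-enrol, divide evenly between arms and keep the full effect into the RCT's 6-month window. The 75% and 70% figures rest on assumed contamination of 5% and 10% and should not be read as what will happen. The point matters because power is at the 80% boundary, so even modest dilution takes it lower.

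**What to change.** Before RCT enrolment opens:

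1. Add to the RCT criteria: did not take part in the focus groups or pilot, and has not previously played the study game. Check this against the study's contact list and ask it at the existing phone check.
2. In the RCT build, keep any sharing rewards and links switched off and limit access to intervention log-ins until the last 6-month assessment is complete.
3. Add one item to the control-arm follow-up surveys asking whether the participant has seen or played the game, so that contamination can be reported. The Measures section lists game use as a survey domain but does not say that controls are asked about the study game.

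The cost is one eligibility line, one build setting and one survey item. At most 74 candidates are lost to recruitment, and the sharing feature is not evaluated in the RCT.

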### Description of Intervention Content

The life-simulation game prototype for smartphones (iOS and Android), tablets, and the web was developed in a phase 1 Small Business Innovation Research study [33] and shows an AYAs’ HIV risk based on their sexual choices in the game. Several areas for modification were identified in the phase 1 study, including the incorporation of a customizable avatar; the development of additional activities, locations, and dating scenarios; incorporation of data analytics features to collect game and paradata; and access to a PrEP provider locator. The incorporation of these modifications has resulted in an enhanced life-simulation game that will be further refined throughout the course of the study (Figure 1). Players can create their in-game *self* using a system that unifies all forms of racial and gender expression into a single avatar, allowing both cisgender and unique transgender and nonbinary characters customized to the player’s specifications. Our previous data suggest that increasing in-game self-expression can result in player identification with their onscreen character, concern for their character’s HIV risk profile, and interest in HIV testing and prevention. The player’s character can seek to date same-sex partners, opposite-sex partners, both, or neither (Figure 2). The game features in-depth dialog for players to explore social interactions for both dating and platonic relationships. Fresh branches of storylines are opened up or shut down based on the player’s choices. The game directly links both rewards and penalties to the player’s choices, which establishes credibility with players that the game is not arbitrary but displays real-life consequences for all their actions. This credibility is necessary for the consequences of their sexual choices to be meaningful and impactful. When the player’s flirtations succeed, a screen appears with their chosen partner and a range of sexual choices based on the sex of the player and their partner [33]. For each sexual act selected, the player is prompted to decide whether to use condoms. When the player clicks *Let’s Get It On*, the player hears romantic music and fireworks burst onto the screen to imply sexual activity, with no graphic content displayed.

After the implied sexual activity, the music abruptly stops, and the player sees the estimated HIV risk their character just incurred (Figure 3). The player is then offered an opportunity to locate low-cost or free HIV testing sites near them by inputting their ZIP code or giving the game permission to read their phone’s location. Data from the US Centers for Disease Control and Prevention testing locator appear with details on where to get tested locally (Figure 4). Although AYAs do not see their HIV risk immediately after a real-life sexual encounter, AYAs in this game are directly confronted by the reality of the risk their character incurs. Our phase 2 study will test whether this system helps reinforce the connection between sex and risk, thereby improving HIV testing.

